##### Isolation and expansion of WJ-MSCs

2.3.1.1

The consenting umbilical cord donor is a lady in labor at the “Al-Amal Maternity Hospital” with blood group O who has been screened for infectious agents (HIV, Syphilis, Hepatitis B and C). Isolation of MSCs from the Wharton jelly is performed using the explant method.^[19]^ All steps are conducted according to good laboratory practice and good cell culture practice principles at the CTC clinical tissue-culture lab. A cell bank generated from a single donor expanded to a clinical grade provides sufficient number of cells to be transplanted to all patients eliminating the donor variability in interpreting treatment outcomes.

The maternal umbilical cord is rinsed with (PBS) (pH7.4) and cut into 2 cm-long pieces and plated in round tissue culture dishes. The explants are allowed to attach for about 15 minutes, then culture medium is gently added to the plates and incubated for 8 days in humidified 5% CO^2^ incubators. Cells are fed with fresh medium every 3 days until individual colonies reach 70% to 80% confluence. After the primary passage, cells are detached using the xenogenic-free10xTriple E (Thermo Life Technologies, ThermoFisher, MA. WJ-MSCs are reseeded at a density of 4 × 10^3^ cells/cm^2^ in 175 cm^2^ flasks and subsequently moved to double layer Nunc Cell Factory Systems (Nunc, Thermo Scientific, Waltham, MA) to reach clinical numbers at passage 3. Cells are cryopreserved and adequate number are thawed and allowed to proliferate to be ready as treatment at passage 4. The conditioned media of WJ-MSCs are stored at –800° C Freezers at the CTC to be used for the third injection.

The expansion culture medium consists of the following: α-modified minimum essential medium (α-MEM; GIBCO, ThermoFisher, MA) supplemented with 10% platelet lysate, 1% (w/v) Penicillin/Streptomycin (P/S) and 2 mM L-glutamine (GIBCO, ThermoFisher, MA). The culture medium is changed twice a week. The quality of WJ-MSCs is examined throughout the expansion steps visually and microscopically for any fungal or bacterial contamination and using Q-PCR for any mycoplasma contaminant prior to patient administration.

##### Characterization of WJ-MSC

2.3.1.2

Characterization of the patients’ expanded MSCs is in accordance with the International Society for Cellular Therapy (ISCT) recommendations.^[20]^ Cells are observed microscopically for the spindle shape and attachment to tissue culture flasks. Flow cytometry is performed to confirm the expression of CD73, CD90, and CD105 surface molecules at a percentage of at least 95% and the absence of CD34, CD45, CD14, and CD3 surface markers at no more than 5%. In addition, the differentiation assessment into adipogenic, osteogenic, and chondrogenic lineages is performed according to the differentiation media manufacturing recommendations; StemPro differentiation media (GIBCO, ThermoFisher, Waltham, MA).

#### Physical therapy exercise) program (control group 2)

2.3.2

The PTE program utilized in this study is partly based on 2 previous published exercise programs that were found to be effective in improving balance and mobility in PwMS.^[7,21]^ Following the physical activity guidelines for adults with MS,^[22]^ we will further add 30 minutes of aerobic exercise to the program. Additionally, we will also follow the guidelines of having a minimum 2 sessions per week of physical activity for PwMS. The PTE program consists of a mixed program including the following types of exercises: balance, resistance, flexibility, and aerobic exercises performed 2 times per week for a total of 6 months. The intensity of the exercise will be progressed throughout the 6 months’ period and consists of 3 stages of progression for the resistance/flexibility and balance programs, and 2 stages of progression for the aerobic exercise program. Participants will be progressed to each stage depending on their tolerance and performance level of the exercises. Each session will take 60 to 80 minutes to finish, and will be supervised by a trained physical therapist (PT). Exercise will be performed in a well-equipped lab space at the CTC at University of Jordan. Following the 6 months supervised program, participants will continue the remaining 6 months of the study period performing a home exercise program (HEP).

The PTE session is divided as the following: pre-exercise vital signs measured using a digital HR/BP monitor, 5-minute warm-up exercises, 10 to 15 minutes of strength and flexibility exercises, 10 to 15 minutes of postural balance exercises, 40 minutes of aerobic exercise on a recumbent stepper machine and a 5-minute cool-down. Vital signs will be taken again post-exercise. Resting periods will be given to each participant before progressing to other forms of exercises and as necessary to decrease levels of fatigue. Participants will be allowed to choose the appropriate days/times to do the sessions upon their convenience but will be encouraged to choose the session every other day to allow a day rest in between. Vital signs, comments, and progress of each session will be documented for every participant using weekly exercise logs.

The warm up/cool down exercises that will be performed before and after the PTE will each take around 5 minutes; all exercises are to be done for 3 to 5 repetitions. The PT will demonstrate and supervises the exercises for the participants. The warm up/cool down exercises include chin tucks, arm circles, shoulder shrugs, marching in place, hamstring stretch, heel cord stretch/calf stretch, knee to chest, heel raises/toe raises, and mini-squats (a chair or wall in front can be used if needed for support). The remaining supervised exercises will be performed in the following order:

##### Resistance and flexibility exercises

2.3.2.1

The following guidelines are followed across the 3 stages: A list of 10 different exercises is given to the participant. The participants are allowed to choose 5 exercises out of the 10 exercises each session with the help of the PT. In case the participant was not able to perform 1 of the exercises, the PT chooses another 1 from the remaining 5 and so on. The participant perform the other 5 exercises the next session and alternate every session accordingly. For the exercises that requires resistance, if the participant cannot perform any of the exercises against resistance using cuff weights, Thera band, etc. The participant is allowed to perform the exercise without resistance until he/she feels comfortable with it and can perform it successfully pain free. The PT will add resistance when participant perform the exercise successfully and pain free. If the participant cannot perform the required number of repetitions, the PT decreases the frequency to the participants’ ability and increase accordingly until reaching the desired outcome. The PT records the exercises/intensity/frequency performed by the participant on the weekly exercise log every session. The resistance and flexibility exercises through the 3 stages are listed in detail in Supplemental Digital Content (Appendix 1).

##### Balance exercises

2.3.2.2

The following guidelines should be followed across the 3 stages: a list of 10 different exercises is given to the participant. The participants are allowed to choose 5 exercises out of the 10 exercises each session with the help of the PT. In case the participant was not able to perform 1 of the exercises, the PT chooses another 1 from the remaining 5 and so on. The participants perform the other 5 exercises the next session and alternate every session accordingly. For the exercises that requires challenges, if the participant cannot perform challenging exercises using: balance board, Swiss ball, dual tasking…etc. The PT will allow the participant to perform the exercise without the challenge until comfortable with exercise, and then add the challenge when participant perform the exercise successfully and safely. The PT will add resistance when participant perform the exercise successfully and pain free. If the participant cannot perform the required number of repetitions, the PT decreases the frequency to the participants’ ability and increase accordingly until reaching the desired outcome. The PT records the exercises/intensity/frequency performed by the participant on the weekly exercise log every session. The balance exercises through the 3 stages are listed in detail in Supplemental Digital Content (Appendix 2).

##### Aerobic exercise

2.3.2.3

The following guidelines are followed across the 2 stages: exercise intensity in stage I is 50% to 59% of heart rate reserve for 3 months; increased to stage II 60% to 69% of heart rate reserve for remaining 3 months. Exercise session total time is 40 minutes on the recumbent stepper supervised by the PT including 5 minutes warm up, 30 minutes aerobic training, and 5 minutes’ cool down. Aerobic exercise is performed on the same recumbent stepper used for the submaximal testing during the baseline assessment (Model SCIFIT-StepOne). The handles and seat is adjusted according to the participant's arm and leg length prior to the exercise session (taken from the submaximal test performed at baseline). Pre and post exercise vital signs (HR and BP) are taken. Heart rate is monitored during the exercise using polar heart rate monitors. Five minutes’ warm-up and cool down on the recumbent stepper is set at 25 watts load at a comfortable pace. Exercise intensity during the 30 minutes’ period is increased to the prescribed target heart rate range that is initially calculated using the Karvonen formula.^[23]^ Intensity is adjusted according to physiologic response but not to exceed the target heart rate range during the 30 minutes’ period. Rate of perceived exertion is monitored before and after the aerobic training period using the Borg scale. During the 30 minutes of exercise, each participant is instructed to keep their stepping pace at 100 steps/min that would be visible for them on the machine monitor. However, each participant is allowed ± 5 steps (95–105 steps/min) during the exercise. The intensity used, vital signs, rate of perceived exertion, and any comments or changes during the session is recorded on a weekly exercise log. After the cool down, participants are allowed ample time to rest before they leave.^[24]^

##### Home exercise program

2.3.2.4

The HEP focuses mainly on the home use of an exercise DVD that was specifically developed for people with movement disorders and available in the Arabic language. Details of the exercise DVD and its content are published elsewhere.^[25,26]^ In brief, this DVD focuses on the main components of fitness introduced by an acting lady and a gentleman in 5 main sections. The first section is focused on warm up and flexibility activities; the second, third, and fourth sections focus on strength, flexibility, balance and endurance exercises, and training on performing functional tasks of sit to stand, stepping up onto stairs, and getting on and off the floor; and the fifth section focuses on relaxation, stretching, and breathing techniques. In addition to these main 3 sections, the DVD includes a list of precautions, equipment required, and postural instructions.

During the HEP, participants are instructed to perform the exercises 2 times a week using the exercise DVD. After the end of the first 6 months of the intervention, the participants will receive 1 instructional session in the CTC from a trained PT. In this session participants are introduced to all exercises in the exercise DVD; the therapist observe the participant while performing the exercises and provide feedback whenever is needed. There is a total of 29 different exercises in the DVD, the participants are encouraged to perform all of them. However, the participant is allowed to choose which exercises to perform if any of the exercise were found difficult to execute or if it was not feasible to perform at their home. Participants should perform at least half of the exercises in the DVD. Each participant will be provided with the DVD along with a hardcopy manual of the exercises. In addition, potential benefits and risks of performing the exercises are discussed. During the instructional session, participants are also instructed on how to progress their exercises by gradually increasing the number of repetitions while decreasing the number and length of rest breaks and increasing the level of exercise progression. In addition, participants will be contacted by the PT every month via phone calls to assess their compliance to the program and document any barriers to exercise of they have any. A predetermined protocol for these instructional sessions is provided in Supplemental Digital Content (Appendix 3). For the remaining period of the program, participants are asked to perform the 2 exercise sessions per week independently at home. Participants are asked to keep an exercise diary for their HEP exercises to assess their compliance to the HEP program. Participants will return the exercise diary at their 1-year post assessment appointment. Supplemental Digital Content (Appendix 4).

#### Combined treatment group (PTE and WJ-MSCs) (experimental group)

2.3.3

In this group, a combined interventions of both the PTE and WJ-MSCs will be administered.

### Outcomes

2.4

On the day of the assessment, each participant performs the measures in the following order: cognitive function assessment, surveys/questionnaires, physical function assessment, biological assessment, and (MRI).

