#### Motor assessment measures

2.4.1

*2.4.1.1. Aerobic fitness* is assessed using the submaximal testing. In this test a seated recumbent stepper (Model SCIFIT-StepOne) will be used, which provides simultaneous movement of the upper and lower extremities in a continuous stepping motion. During the submaximal exercise test, the participants are asked to move their arms and legs in an alternating pattern at a constant speed of 100 steps per minute and resistance (Watts) will be increased every 3 minutes according to the total body recumbent stepper submaximal exercise test until 85% of age-predicted heart rate max is met or participant can no longer continue due to fatigue (test termination endpoint). During the test, heart rate is monitored using polar heart rate monitors. Ten seconds prior to the end of every stage, heart rate is taken and recorded. Once the test is finished, the participant will continue to step at a comfortable self-selected speed with minimal resistance for 2 minutes or until heart rate returns to near baseline levels.^[27]^ The outcome measure is predicted VO2 max calculated by a formula using the participant age, sex, weight, watts used, and HR.^[27]^

*2.4.1.2. Balance and mobility* are assessed using the following assessment tools:

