1.6-minute walk test will be used to assess physical endurance capacity.^[28]^ This test needs a hallway with 2 cones 15 meter apart to be performed. The participant walks between the 2 cones for 6 minutes. Distance is measured by number of laps to be completed.2.The Arabic version of the dynamic gait index will be used to examine gait performance and the likelihood of falling ^[29]^. The dynamic gait index has been translated to several languages including the Arabic language.^[30]^3.The Arabic version of the Berg balance scale will be used to assess static balance.^[31]^ It consists of 14 common functional activities that occur in everyday life.^[32]^4.Timed-Up and go test is a test for assessing balance and walking ability.^[33]^ The participant is instructed to rise from a chair, walks 3 meters at a comfortable and safe pace, turns, walks back to the chair, and sits down. The time between the start of the test until the participant sits back on the chair is recorded and used as the outcome measure.5.The Arabic version of the activities-specific balance confidence scale will be used to detect balance confidence.^[31]^ This scale was found to be both reliable and valid for the assessment of balance in PwMS.^[34,35]^6.Barthel index is a self-reported questionnaire that evaluates the ability of individuals to perform activities of daily living and mobility activities ^[36]^. The BI is considered as a measure of disability that had good reliability and validity ^[36,37]^. The BI has been used with individuals with neurological disorders.^[38]^

2.4.1.3. *Upper extremity motor function (UEMF)* is assessed using the following tests:

1.Grip strength of the participants will be assessed using a hand held dynamometer (Model Jamar hydraulic hand dynamometer).^[39]^ Each participant will be instructed to squeeze the handle with maximum strength first on the dominant hand and then on the non-dominant hand. Three trials on each hand will be performed. The average maximum force exerted from the 3 trials will be used as a primary outcome measure.2.9-hole peg test is a specific test for finger dexterity.^[40]^ The participant is asked take pegs from a container, one by one and put them into holes. Then take the pegs back from the hole, one by one an out them into the container as quickly as possible. The time taken to finish the task will be recorded and used as an outcome measure. The test will be performed first on the dominant hand then on the non-dominant hand.

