##### Biological markers

2.4.3.1

Bio-specimens including blood and cerebrospinal fluid are collected from participants by a trained nurse. Inflammatory markers in the blood are examined using Multiplex ELISA technology. Neural regeneration markers will be measured in the CSF and blood collected. Tests will be performed by CTC biotechnologists. Moreover, the percentage of T, B and NK cells in the blood of participants will be calculated at the CTC flow cytometry lab by a dedicated biotechnologist. Additionally, the IgG levels in the CSF will be measured in a referral CAP accredited lab (MEDLAB).

The difference in concentrations compared to baseline measurements of biomarkers in the blood and CSF of patients in pg/mL enables the evaluation of the inflammatory and neural regeneration/degeneration status in response to interventions. While a change in the percentages of the different immune cells in participant's blood is an indication of immune-modulation outcome.

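### The fixed test-day order puts blood sampling after graded exercise, so the immune and inflammatory markers are not resting values, and comparisons of exercise-trained with untrained participants may be biased

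*Protocol article*

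**What the plan says.** Section 2.4 (Outcomes) of the protocol article sets one sequence for the assessment day: "each participant performs the measures in the following order: cognitive function assessment, surveys/questionnaires, physical function assessment, biological assessment, and (MRI"). Sections 2.4.3.3 and 2.5 move MRI to a separate day. Nothing moves the blood sample.

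Section 2.4.1 (Motor assessment measures) describes what comes before the sample:
- **Stepper test.** The load is stepped up: "resistance (Watts) will be increased every 3 minutes according to the total body recumbent stepper submaximal exercise test". The test runs "until 85% of age-predicted heart rate max is met or participant can no longer continue due to fatigue". Afterwards the participant steps easily "for 2 minutes or until heart rate returns to near baseline levels".
- **Walk test.** "The participant walks between the 2 cones for 6 minutes".
- **Other tests.** Gait, balance, grip and dexterity tests are in the same section.

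Section 2.4.3.1 (Biological markers) states: "Bio-specimens including blood and cerebrospinal fluid are collected from participants by a trained nurse". Blood is used for inflammatory markers and for T, B and NK cell percentages. Differences in concentration from baseline are used to judge the inflammatory state in response to the interventions, and "a change in the percentages of the different immune cells in participant's blood is an indication of immune-modulation outcome".

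The measures are repeated at 3, 6 and 12 months (2.5). The aerobic part of the exercise programme uses the stepper model on which participants are tested, at the same stepping rate (2.3.2.3). The analysis covers within-group and between-group change (2.9).

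**The concern.** A marker read as evidence of treatment response should be sampled under conditions that are standard across people and visits. For blood cell percentages and inflammatory markers, the natural standard is rest. The written order gives a post-exertion sample instead. The exertion is not a fixed dose, because the stepper test stops at a heart-rate or fatigue limit and fitter participants may complete more stages.

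Two things are at stake. The first is precision: load and time from test to needle vary between people and visits, which adds noise with only 20 participants per arm. The second is possible bias. Two of the three arms train on the test device for six months and one does not. If the acute response depends on the work done, part of an apparent change in immune markers could come from the test and not from the treatment. This cannot be removed in analysis once the samples have been taken.

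**Working it through.** The plan gives no figure to reproduce. The check is a reading of the sequence, then the bias algebra, then an illustration under stated assumptions.

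**1. Sequence.** 2.4 puts physical function directly before biological assessment. I take physical function to mean the tests under 2.4.1, which is headed as motor measures. The battery lasts about 2 to 3 hours (2.5), so blood is drawn within hours of the stepper test at most. The order of tests within the physical block is not stated, so the exact gap is unknown.

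**2. Algebra.** Let *a* be the mean acute shift in a marker due to exertion before the draw, by arm and visit. For arms A and B:

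observed difference in change = true effect + [(*a* at follow-up − *a* at baseline) in A − (*a* at follow-up − *a* at baseline) in B].

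Randomisation makes the baseline shifts equal in expectation, so the bracket reduces to follow-up *a* in A minus follow-up *a* in B.

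- Same shift in all arms and at all visits: the bracket is 0 and within-arm change is also unaffected.
- Same shift in all arms but varying by visit: the between-arm bracket is 0, but within-arm change is affected.
- Shift dependent on training: the bracket need not be 0 for combined versus WJ-MSCs alone or PTE versus WJ-MSCs alone. Within-arm change in the two exercise arms is also affected.
- Combined versus PTE alone: both follow the same exercise programme (2.3.2, 2.3.3), so the documents give no mechanism for a non-zero bracket.

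**3. What a differential shift would do.** Inputs from the article: 20 per arm (1.2) and alpha 0.05 (2.9), taken as two-sided. Assumptions: no true effect, a pairwise two-sample t-test (df = 2 × 20 − 2 = 38) as a stand-in for the planned analysis of variance, and a between-arm difference in acute shift of *d* SD of the change score. The noncentrality is *d* × √(20/2) = 3.162*d*.

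| Assumed *d* | Noncentrality | Probability of a false positive |
|---|---|---|
| 0 | 0 | 5.0% |
| 0.1 | 0.316 | 6.1% |
| 0.2 | 0.632 | 9.5% |
| 0.3 | 0.949 | 15.2% |
| 0.5 | 1.581 | 33.8% |
| 0.8 | 2.530 | 69.3% |

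The documents give no value for *d*. This is a range and not an estimate.

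**4. Why percentages are sensitive.** Assume resting shares of T 75%, B 13% and NK 12%, and that exertion multiplies NK counts by *k* and T counts by *t*, with B unchanged. Then NK share = 12*k* / (75*t* + 13 + 12*k*), and B share = 13 over the same denominator.
- *k* = 1.5, *t* = 1.1: NK 18/113.5 = 15.9%; B 13/113.5 = 11.5%.
- *k* = 2, *t* = 1.2: NK 24/127 = 18.9%; B 13/127 = 10.2%.
- *k* = 3, *t* = 1.3: NK 36/146.5 = 24.6%; B 13/146.5 = 8.9%.

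All these inputs are assumptions. They show that a rise in one cell type moves the shares of the others. They describe the total acute shift, and any part of it that is common to the arms cancels between them.

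**The case against.** The strongest reply is that the order is identical for everyone at every visit, so a common shift cancels between arms and a stable one also cancels in change from baseline. That is correct, and it limits the point. A reader might infer that the markers are distorted by a different amount in each arm. The documents do not support this: they do not show that the acute response differs by arm, and they give no reason for the two exercise arms to differ from each other.

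Second, a heart-rate limit partly equalises relative effort, and completing more stages does not prove a larger immune response. This also stands, so neither size nor direction can be claimed. The stepper argument weakens at month 12, because supervised training ends at month 6 and a home DVD programme follows (2.3.2, 2.3.2.4).

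Third, the stepper test has a cool-down, other tests may fall between it and the needle, and sampling conditions are detail that an article may leave to the full protocol. This stands in part. The gap is unknown and the absence of a laboratory procedure is no fault. The point rests on something else: the article does state an order, and that order puts exertion before blood.

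Fourth, the stated hypothesis concerns motor and non-motor symptoms (1.1), and cell percentages are called only an indication. This is fair, and it confines the consequence to the blood markers.

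**Conclusion.** The concern holds in limited form. By the written order, blood is a post-exertion sample and not a resting one, while 2.4.3.1 reads its change as response to intervention. Varying test load and test-to-draw time add noise in all arms. Bias is possible in within-group change in the two exercise arms and in comparing either with WJ-MSCs alone, mainly at months 3 and 6. Combined versus PTE alone has no stated mechanism for bias.

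The size and direction are unknown. The false-positive range (5.0% at no differential shift, 15.2% at 0.3 SD, 33.8% at 0.5 SD) depends on assumed shifts. The conclusion also assumes that exertion of this kind acutely alters these markers, which is general physiology and is not quantified in the article. It would be wrong to infer that the trial's motor and non-motor conclusions are affected: the problem is confined to the blood markers. It is worth correcting because the change is cheap and the loss cannot be recovered later.

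**What to change.** In 2.4 (Outcomes), specify that the blood sample is drawn at the start of the visit, after seated rest and before any physical testing, at baseline and at months 3, 6 and 12. Schedule each visit on a day without a training session. Limit the change to blood: leave CSF collection and the rest of the order where they are.

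The cost is reordering one step, with no new procedure or visit. There are two small downsides. Venepuncture would come before the cognitive tests, questionnaires, grip strength and peg test. Grip matters here because 2.4.1.3 labels it a primary outcome measure, but the effect would be equal in all arms. Blood and CSF would also be collected at separate points in the visit.
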